### Data collection procedure

2.8

Baseline assessments will be conducted face-to-face at the company’s facilities. Questionnaire-based outcomes will be completed on paper under the supervision of a member of the research team, while physical tests will be administered by qualified professionals following standardized protocols.

All outcome measures, except for baseline sociodemographic data, will be reassessed immediately after completion of the intervention and at a one-month follow-up, using identical assessment protocols, time schedules and, where possible, by the same assessor.

All collected data will be anonymized and coded using a unique identification number assigned to each participant. Personal identifying information will be stored separately from research data and will be accessible only to the principal investigator. Paper-based questionnaires will be kept in locked cabinets at Universidad San Jorge, and electronic data will be entered into a password-protected database hosted on secure institutional servers compliant with European data protection regulations (GDPR and Spanish Organic Law 3/2018). Data entry will be double-checked to minimize transcription errors, and range and consistency checks will be performed prior to statistical analysis. Data will be retained for 5 years following study completion and then securely destroyed.

Figure 2 presents the study timeline and key procedural details.

**Figure 2 fig2:**
[figure not shown]
Study timeline.

### Sample size

2.9

Based on previous studies conducted in industrial worker populations evaluating similar interventions, a minimum clinically important difference of 1.5 points on the NRS for pain was assumed, together with a standard deviation of 2.5 points (36, 37). Using a two-sided *α* level of 0.05 and a statistical power of 80%, the required sample size for a paired-sample comparison was estimated to be 27 participants (Cohen’s d = 0.60). Accounting for an anticipated 20% attrition rate, the final adjusted target sample size was set at 33 participants. The computation was performed using Jamovi (version 2.7.6; www.jamovi.org), specifically the power analysis module for paired-sample *t*-tests.

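### Section 2.9's sample-size figures do not follow from its stated inputs: 80% power at d = 0.60 needs 24 pairs, not 27, and 20% attrition on 27 gives 34, not 33

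*Protocol article*

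**What the plan says.** Section 2.9 (Sample size) of the protocol article gives all inputs and both results in one paragraph. For the effect, "a minimum clinically important difference of 1.5 points on the NRS for pain was assumed", "together with a standard deviation of 2.5 points", which the text turns into a Cohen's d of 0.60. The test is two-sided at 0.05 with 80% power, and the software used is named as "specifically the power analysis module for paired-sample *t*-tests". The first result is that "the required sample size for a paired-sample comparison was estimated to be 27 participants". The second is: "Accounting for an anticipated 20% attrition rate, the final adjusted target sample size was set at 33 participants".

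Two other sections bear on how the result is read. Section 2.6.2 (Primary outcome) defines the primary outcome as the change in pain score from baseline to post-intervention, which fits a paired comparison. Section 2.10 (statistical analysis) makes the primary analysis per-protocol, restricted to participants who attended at least 80% of planned sessions. It analyses three time points by repeated-measures ANOVA or the Friedman test, with Bonferroni-adjusted pairwise comparisons.

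**The concern.** The inputs and the results stand side by side, so the calculation can be repeated, and it does not give the printed numbers. The required number is larger than the stated power calls for, and the enrolment target is smaller than the stated requirement and attrition call for. At least one printed figure (the power, the effect size, the SD or the number) is therefore not the one used. Condensing a full protocol into an article does not explain a disagreement within a single paragraph.

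At stake is the traceability of the planned power. The stated power also becomes the benchmark against which a later null or borderline result is read, so it should be right for the analysis that will be run.

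**Working it through.** **Inputs (all from section 2.9).** Difference 1.5; SD 2.5; d = 1.5/2.5 = 0.60; two-sided alpha 0.05; power 80%; paired t-test; attrition 20%. The paragraph does not say whether 2.5 is the SD of within-person change or of raw scores. Dividing 1.5 by it directly to get the d for a paired test treats it as the SD of change, and the check does the same.

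**Step 1: the required number.** For n pairs, the test statistic has n − 1 degrees of freedom and noncentrality d√n. Power is the probability that its absolute value exceeds the 97.5% point of the t distribution.

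| n pairs | Power at d = 0.60 |
|---|---|
| 23 | 78.5% |
| 24 | 80.4% |
| 26 | 83.6% |
| 27 | 85.1% |

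The smallest n reaching 80% is 24. As a cross-check, the normal approximation is ((1.960 + 0.842)/0.60)² = 21.8. Adding the usual small-sample term 1.960²/2 = 1.92 gives 23.7, again 24.

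**Step 2: can 27 be recovered?** Variants tried at 80% power and d = 0.60:

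- one-sided paired t-test: 19
- normal approximation: 22
- alpha 0.05/2: 29
- alpha 0.05/3: 32

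None gives 27. Two changes of input do: 85% power at d = 0.60, or a d of about 0.56 at 80% power. A third route is to treat 2.5 as a raw-score SD. The paired effect is then 0.60/√(2(1 − r)), and 27 results when the pre–post correlation r is about 0.43 to 0.44. The article states no correlation and gives d as 0.60, so this cannot be confirmed.

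**Step 3: attrition.** To keep 27 after 20% loss, enrol 27/(1 − 0.20) = 33.75, so 34. Working back from the stated target, 33 × 0.80 = 26.4, so about 26 remain, one fewer than the stated 27. For a requirement of 24, the target would be 24/0.80 = 30.

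**Step 4: what 33 delivers.** With 26 completers and d = 0.60, power for the unadjusted two-sided paired t-test is 83.6%.

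**Step 5: what that 83.6% leaves out.** The documents give no expected adherence rate, so the rates here are assumptions. Among 26 completers, 90% adherence leaves 23.4, about 23 (78.5% power); 80% leaves 20.8, about 21 (74.4%). Separately, if the baseline to post-intervention contrast has to pass the Bonferroni rule, 26 evaluable participants give 74.6% at alpha 0.05/2 and 68.8% at alpha 0.05/3. Section 2.10 does not state the divisor.

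**The case against.** The strongest reply is that the error lies on the safe side. The stated requirement exceeds the true minimum by 3, and the target of 33 exceeds the 30 needed for 24 completers. Even 26 completers exceed the stated 80% for the comparison that section 2.9 describes. This stands. A reader might infer from the wrong figures that the trial is underpowered; for the unadjusted paired comparison after attrition alone, the documents do not support that.

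The gap between 33 and 34 is one participant and would hardly merit comment alone. That also stands. A reader might further infer that the target came from multiplying 27 by 1.2 (32.4, rounded up). The article shows no formula, and rounding 33.75 down also gives 33, so the cause is unknown.

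Nor is it right that the reader cannot tell which comparison was meant: the test, the difference and the primary contrast are all named. Finally, the per-protocol and Bonferroni figures do not show that 27 or 33 was miscalculated. They rest on an assumed adherence rate and an unstated divisor, so neither 74.4% nor 68.8% can be quoted as the trial's power. They show only that the 84% is conditional, which the restated paragraph should say.

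What the reply does not remove is the disagreement itself. Nothing elsewhere in the article explains 27 at 80% power.

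**Conclusion.** The point holds as a reporting error in section 2.9. The stated inputs require 24 pairs; the printed 27 corresponds to 85.1% power, or to d of about 0.56 at 80%. Keeping 27 after 20% attrition needs 34 enrolled; the printed 33 leaves about 26.

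The consequence is limited. With 2.5 taken as the SD of within-person change, the enrolment target supports about 84% power for the unadjusted baseline to post-intervention paired t-test, so the target need not change on this account. That margin is small. It assumes that every completer meets the 80% attendance rule and that the primary contrast is tested at the full 5% level. At 90% adherence among completers, power already falls just below 80%.

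**What to change.** Keep the enrolment target at 33 and rewrite the paragraph in section 2.9:

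1. State that 33 enrolled with 20% attrition leaves about 26 evaluable, giving about 84% power for d = 0.60 with an unadjusted two-sided paired t-test at 0.05.
2. State whether 2.5 is the SD of within-person change or of raw scores. If raw, give the pre–post correlation used and the resulting paired effect size.
3. State that this power assumes no further loss from the per-protocol rule in section 2.10. If that set stays primary, give the power over an assumed adherence range, for example about 23 evaluable and 78.5% at 90% adherence, and about 21 and 74.4% at 80%.
4. If the primary contrast is tested under the Bonferroni post-hoc rule, state the divisor and the power: with 26 evaluable, 74.6% for two comparisons or 68.8% for three.

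These are changes of wording, with no change to enrolment or procedures. Two other consistent statements are possible: 24 evaluable and 30 enrolled for 80% power, or 27 evaluable and 34 enrolled for 85%. Both alter the enrolment target, so they are more than a correction of text.

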### Statystical analysis

2.10

The statistical analysis of the quantitative data will be performed using IBM-SPSS Statistics version 29 (IBM Corp., Armonk, NY, United States). Data will be expressed as the mean and the standard deviation with a 95% confidence interval or as the median and the interquartile range. The Shapiro–Wilk test will be used to assess normality.

Given the longitudinal design with three assessment points (baseline, post-intervention, and one-month follow-up), changes over time will be analysed using repeated-measures analysis. When parametric assumptions are met, a repeated-measures ANOVA will be conducted, with post-hoc pairwise comparisons adjusted using the Bonferroni correction.

For non-parametric data, the Friedman test will be used to assess overall changes over time, with post-hoc pairwise comparisons conducted using Wilcoxon signed-rank tests, and *p*-values adjusted using the Bonferroni correction.

Effect sizes and 95% confidence intervals will be reported to quantify the magnitude of observed changes, using eta squared (η^2^) for ANOVA analyses and Kendall’s W for Friedman tests, in addition to *p*-values.

The primary analysis will follow a per-protocol approach, including only participants who attended at least 80% of the planned intervention sessions, as defined by the adherence criteria.

Statistical significance will be set at *p* < 0.05.

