#### Primary outcome

2.6.2

*Pain intensity:* Pain intensity will be measured using the Numeric Rating Scale (NRS), an 11-point validated self-reported measure widely used in musculoskeletal and occupational health research. Participants will be asked to rate their average musculoskeletal pain on a scale ranging from 0 (no pain) to 10 (worst imaginable pain) during face-to-face assessment sessions.

The NRS has demonstrated good reliability, validity, and responsiveness to change in musculoskeletal populations. Scores are commonly interpreted as: mild pain (1–3), moderate pain (4–6), and severe pain (7–10) (17).

The MCD for the NRS in musculoskeletal pain has been estimated at 1.5–2 points, which will be used to interpret the clinical relevance of pre–post changes (18). The primary outcome will be the change in NRS scores from baseline to post-intervention.

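### The primary NRS outcome is the T0–T1 change in points, but the planned three-visit ANOVA/Friedman analysis, chosen by a normality test, does not name that change with its 95% CI as the primary estimate

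*Protocol article*

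**What the plan says.** Section 2.6.2 (Primary outcome) fixes the contrast: "The primary outcome will be the change in NRS scores from baseline to post-intervention". It gives a threshold of 1.5–2 NRS points, "which will be used to interpret the clinical relevance of pre–post changes".

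Section 2.9 (Sample size) is built on the same contrast, as a paired t-test: "a minimum clinically important difference of 1.5 points on the NRS for pain was assumed", "together with a standard deviation of 2.5 points". It arrives at 27 participants, raised to 33 for 20% attrition.

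Section 2.10 (statistical analysis) uses Shapiro–Wilk to assess normality and then sets two branches over the three visits:
- "When parametric assumptions are met, a repeated-measures ANOVA will be conducted", with Bonferroni-adjusted pairwise comparisons.
- "For non-parametric data, the Friedman test will be used to assess overall changes over time", with Bonferroni-adjusted Wilcoxon signed-rank pairs.

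It adds that "Effect sizes and 95% confidence intervals will be reported to quantify the magnitude of observed changes" and names eta squared for the ANOVA and Kendall's W for Friedman. Data are to be summarised as mean and SD with a 95% CI, or as median and interquartile range. The primary analysis is per protocol, at 80% attendance or more.

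**The concern.** Sections 2.6.2 and 2.9 ask whether mean pain fell between T0 and T1, and by how many points. Section 2.10 answers whether the three visits differ at all. T0–T1 enters only as one of three adjusted post-hoc pairs, and no estimate of it is singled out. Three consequences follow.

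- **Effect size.** The two named measures pool all three visits, carry no direction and have no units. They cannot be set against 1.5–2 points.
- **Missing T2.** Both omnibus tests need all three visits, and so do the ANOVA's pairwise comparisons as standard software runs them. A participant whose primary data are complete can be lost because a later visit was missed.
- **Switch.** A data-dependent normality test decides whether the primary result concerns means or ranks.

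**Working it through.** **Plan's own figure.** d = 1.5/2.5 = 0.60. With an exact paired t-test, two-sided 0.05 and 80% power, n = 24 (normal approximation 22). The stated 27 corresponds to 85% power (0.851 at n = 27). For attrition, 27 × 1.2 = 32.4, giving 33; 27/0.80 = 33.75 would give 34. So 27 is more than an unadjusted paired test needs, and this discrepancy is a separate matter.

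**1. Named effect sizes against the outcome.** Take three sets of visit means (T0, T1, T2), with a baseline of 5 or 3.5 as illustration:
- (5, 3.5, 3.5), a fall of 1.5 at T1: grand mean 4, squared deviations 1 + 0.25 + 0.25 = 1.5.
- (3.5, 5, 5), a rise of 1.5 at T1: grand mean 4.5, squared deviations 1 + 0.25 + 0.25 = 1.5.
- (5, 5, 3.5), no T0–T1 change: grand mean 4.5, squared deviations 0.25 + 0.25 + 1 = 1.5.

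The between-visit sum of squares is the same each time, so with equal residual variation eta squared is too. Kendall's W is built from squared deviations of visit rank sums and is equally undirected. A CI for the mean change does answer the question. With a change SD of 2.5 and n = 27, its half-width is t(0.975, 26) × 2.5/√27 = 0.99, so an observed fall of 1.5 would run from 0.51 to 2.49 points.

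**2. Loss of T0–T1 completers.** Of 33, a 20% loss is 6.6. If half falls after T1 (assumption), 33 − 3.3 = 29.7 have T0 and T1, and 33 − 6.6 = 26.4 have all three visits. Paired power at d = 0.60 and alpha 0.05:

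| n | power |
|---|---|
| 30 | 0.888 |
| 29 | 0.877 |
| 26 | 0.836 |

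Another pattern: T1 and T2 each missed independently with probability m. T0–T1 pairs number 33(1 − m) and complete cases 33(1 − m)². For m = 10%, 15% and 20% that is 29.7 against 26.7, 28.1 against 23.8, and 26.4 against 21.1.

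**3. Bias and precision.** Simulation of 33 people and three visits, visit SD 2.5, correlation 0.5 (assumed), true T0–T1 change −1.5, 20% with missing data, 1,500 runs per scenario. Complete cases are compared with a likelihood model with unstructured covariance:

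| Missing | Mechanism | Complete cases, mean (SE) | Likelihood model, mean (SE) |
|---|---|---|---|
| T2 only | random | −1.49 (0.475) | −1.49 (0.425) |
| T2 only | depends on observed T0–T1 change | −2.07 (0.469) | −1.49 (0.436) |
| T1 and T2 | random | −1.50 (0.505) | −1.50 (0.494) |
| T1 and T2 | depends on baseline | −1.23 (0.479) | −1.52 (0.488) |

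In row 2, those who improved less were likelier to miss T2: the selection weight rises by exp(0.5) = 1.65 per point of change, a strong assumed mechanism.

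**4. Frequency of the switch.** Simulated integer NRS limited to 0–10, SD 2.5, correlation 0.5, T1 mean 1.5 lower, n = 27. Shapiro–Wilk on raw scores, counting rejection at T0 or T1, rejects in about 35%, 75% and 98% of samples for baseline means 5, 4 and 3. On T1 − T0 differences it rejects in about 12–21%. Section 2.10 does not say which is tested. Section 2.3 sets no minimum pain score, so low baseline means are possible, but the protocol gives none.

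**The case against.** Repeated-measures ANOVA or Friedman with post-hoc pairs is a conventional plan for a small, single-arm preliminary study. Several limits on the criticism stand.

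- A reader might infer that no result in NRS points will be reported. The text does not support that. Section 2.10 promises means with 95% CIs and pairwise comparisons, and section 2.6.2 intends to read pre–post changes in points. What is absent is the T0–T1 mean change with its CI as the designated primary estimate.
- A reader might infer that everyone missing a visit is discarded. The protocol does not say so. Case deletion follows from how the tests run; imputation is neither planned nor excluded, and a condensed article may leave it to a fuller plan. In the Friedman branch the Wilcoxon pairs need only two visits, so T0–T1 completers can stay in that contrast.
- The power loss is modest and stays above the planned 80%. The figures use alpha 0.05, not the Bonferroni level of the planned pairs; at 0.05/3 power is 0.69 at n = 26 and 0.82 at n = 33.
- The scale's floor cannot be said to set the branch, since rejection on changes is far rarer. Simulated paired t and Wilcoxon tests at the Bonferroni level agreed on significance in about 95–96% of samples.

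None of this removes the mismatch, which lies in what section 2.10 affirmatively names: the tests, the switch and the effect measures.

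**Conclusion.** The concern holds as a mismatch between the stated primary outcome and the stated analysis. It should be corrected, but it does not invalidate the trial. That the named effect sizes cannot be compared with 1.5–2 points, and that the T0–T1 mean change with CI is not designated, follows from the text without assumptions.

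The loss of T0–T1 completers applies to the omnibus tests and the ANOVA branch. It costs about 4–5 percentage points of power if half the attrition falls after T1. The possible bias (−2.07 against a true −1.5 in the strongest scenario) depends on an assumed mechanism and correlation, and shows what could happen rather than what to expect. The normality switch makes the target of inference data-dependent, at a rate anywhere from about 12% to 98% according to what is tested and the assumed baseline mean.

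It would also go too far to see a mixed model as a complete remedy. It adds almost no precision when dropouts miss T1 at random as well (SE 0.494 against 0.505), and it does not bring back participants excluded by the 80% attendance rule, which is a separate issue.

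**What to change.** Prespecify one primary model for NRS in section 2.10:
- A linear mixed model (MIXED in SPSS, the software already named) on all available NRS values, with visit as a categorical fixed effect and unstructured within-person covariance.
- Primary estimate: the T0–T1 mean change in points with its 95% CI, interpreted against the 1.5–2 point threshold of section 2.6.2.
- No Shapiro–Wilk switch for the primary outcome; the Wilcoxon signed-rank test on T0–T1 kept as a sensitivity analysis.

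The cost is a change of wording and slightly more analysis work, with the same software and data and no extra participants or visits. The model's use of partial data is valid if missingness depends only on observed values.

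### The primary baseline-to-week-8 pain change is sized as one paired t-test at 0.05 but analysed as one of three Bonferroni-adjusted comparisons, so the stated 80% power is not delivered

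*Protocol article*

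**What the plan says.** Three sections bear on the test of the primary outcome.

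- **Primary outcome (2.6.2)** fixes one outcome and one time point: "The primary outcome will be the change in NRS scores from baseline to post-intervention".
- **Sample size (2.9)** sizes that contrast as a single paired comparison. On the effect, "a minimum clinically important difference of 1.5 points on the NRS for pain was assumed", "together with a standard deviation of 2.5 points", which the section expresses as Cohen's d = 0.60. With two-sided alpha 0.05 and 80% power, "the required sample size for a paired-sample comparison was estimated to be 27 participants". The target is then raised to 33 for 20% attrition. The tool was Jamovi, "specifically the power analysis module for paired-sample *t*-tests".
- **Statistical analysis (2.10)** analyses change over the three assessments. When parametric assumptions are met, "a repeated-measures ANOVA will be conducted, with post-hoc pairwise comparisons adjusted using the Bonferroni correction". Otherwise a Friedman test is followed by Bonferroni-adjusted Wilcoxon signed-rank tests. Significance is set at p < 0.05.

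Section 2.10 gives no separate test for the T0–T1 change and does not exempt it from the adjustment. Section 2.9 does not carry the adjustment into the sample size.

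**The concern.** The test that was sized is not the test that is planned. Three visits produce three pairs (T0–T1, T0–T2, T1–T2). A Bonferroni adjustment over them compares each unadjusted p-value with 0.0167, or equivalently compares three times the p-value with 0.05. The primary contrast carries that penalty although section 2.6.2 has already reduced the primary question to one outcome at one time point, where a single test needs no multiplicity correction.

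Two things are at stake. First, the study has a materially lower chance than stated of detecting the change it calls clinically important. Second, the text leaves room to report either an adjusted or an unadjusted T0–T1 p-value. If the unadjusted value falls between 0.0167 and 0.05, that choice alone decides whether the primary result is called significant, and it could be made after the data are seen.

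**Working it through.** **Inputs from section 2.9:** difference 1.5 points; SD 2.5 points; d = 1.5/2.5 = 0.60; two-sided alpha 0.05; power 80%; 27 evaluable; 20% attrition; 33 enrolled. **From section 2.10:** three visits, hence 3 pairs, and a per-comparison alpha of 0.05/3 = 0.0167.

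**Formula.** For a paired t-test with n pairs, the test statistic follows a noncentral t distribution with n − 1 degrees of freedom and noncentrality d√n. Two-sided power is P(|T| > t(1 − α/2, n − 1)).

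**Step 1: the protocol's own figure.** The normal approximation gives n = (1.960 + 0.842)²/0.60² = 21.8, so 22. The exact calculation gives 24 (power 80.4%). The stated 27 does not follow from its own inputs; it is 3 more than they require. The error is in the safe direction and is credited to the plan below. For attrition, 27 × 1.2 = 32.4, so 33; dividing by the retention rate gives 27/0.8 = 33.75, so 34. Conversely, 33 × 0.8 = 26.4, so about 26 evaluable are expected.

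**Step 2: power at the sized and at the planned significance level (d = 0.60).** For n = 27 the noncentrality is 0.60 × √27 = 3.118. The critical value is 2.056 at alpha 0.05 and 2.559 at alpha 0.0167.

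| Evaluable n | Power at 0.05 | Power at 0.0167 |
|---|---|---|
| 24 | 80.4% | 64.1% |
| 26 | 83.6% | 68.8% |
| 27 | 85.1% | 70.9% |
| 31 | 89.8% | 78.4% |
| 32 | 90.8% | 80.0% |
| 33 | 91.6% | 81.5% |

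The adjustment costs 85.1 − 70.9 = 14.2 points at n = 27 and 83.6 − 68.8 = 14.8 points at n = 26. Against the stated 80%, the shortfall is 9.1 and 11.2 points.

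**Step 3: size needed under the adjustment.** 80% power at 0.0167 needs 32 evaluable, which is 32/0.8 = 40 enrolled.

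**Step 4: if the pairwise tests also depend on a significant overall F.** Section 2.10 does not say whether they do, so this is an added assumption. A simulation (20,000 runs per case, compound symmetry, SD of the paired difference 2.5, T2 reduction of 0, 0.75 or 1.5 points) gives about 68–69% at n = 26 and about 70% at n = 27. The condition removes little further power; nearly all the loss comes from Bonferroni.

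**Step 5: dependence on what the SD means.** The stated d = 0.60 treats 2.5 as the SD of the paired difference. If 2.5 were instead the SD of a single score (an assumption), the SD of the difference would be 2.5 × √(2(1 − r)), where r is the T0–T1 correlation. At n = 27:

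| r | d | Power at 0.05 | Power at 0.0167 |
|---|---|---|---|
| 0.3 | 0.51 | 71.8% | 53.8% |
| 0.5 | 0.60 | 85.1% | 70.9% |
| 0.6 | 0.67 | 91.8% | 81.5% |
| 0.7 | 0.77 | 97.2% | 92.0% |

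**The case against.** The best case for leaving the text alone has four parts.

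- **The mismatch is conservative.** It cannot inflate the type I error or bias the estimate, and the protocol calls the study preliminary, reports effect sizes and confidence intervals, and reads the change against a clinical threshold. This is true, and it limits the harm to lost power. It does not make the stated power correct.
- **Adjusting across visits is defensible.** The Introduction expects improvement at post-intervention and at follow-up, and pain is measured at all three visits. A team may choose to control error over all pain comparisons. That choice is legitimate, but the sample size must then use the same significance level, and section 2.9 does not.
- **Section 2.10 is a general paragraph for all outcomes.** A fuller plan might treat the primary contrast separately. That is possible, but the published text points the other way: it describes one analysis and exempts nothing. If separate treatment was intended, one sentence settles it.
- **There is slack in the numbers.** The stated 27 exceeds the 24 its inputs require, and 33 will be enrolled. The first surplus is already included in the 70.9%. The second restores 80% only if at least 32 of the 33 are evaluable, which contradicts the planned 20% attrition. The primary analysis is also restricted to participants attending at least 80% of sessions, which can remove people beyond those who drop out.

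The dependence on the SD stands as a caveat. Depending on the correlation, the shortfall could disappear or grow.

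**Conclusion.** The concern holds. As written, the primary contrast is tested at an effective 0.0167 while the sample size assumes 0.05. On the protocol's own effect size, power is 70.9% at 27 evaluable participants and 68.8% at 26, so the chance of missing a true 1.5-point reduction is about 29–31% rather than 20%. These figures rest on d = 0.60, that is, on 2.5 being the SD of the paired difference, and on Bonferroni covering all three pairs. They do not depend on the pairwise tests being conditional on the overall F. The Friedman/Wilcoxon branch has the same mismatch, since its pairwise tests carry the same adjustment; its power was not computed. The false-positive risk is not increased.

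**What to change.** In section 2.10, state that the T0–T1 change in NRS is the single primary test, at two-sided 0.05, without Bonferroni adjustment and not conditional on the overall time effect. Say the same for the non-parametric branch. Make the overall time effect and the T0–T2 and T1–T2 comparisons secondary, and keep Bonferroni there. Power for the primary test is then 85.1% at 27 evaluable and 83.6% at 26, and its type I error remains 5%. The cost is a wording change, to be made before outcome data are examined; no extra participants are needed.

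If the adjustment is to stay on the primary contrast, either restate the power in section 2.9 as about 69–71%, or size at 0.05/3, which needs 32 evaluable and 40 enrolled.

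In either case, section 2.9 should say that 2.5 is the SD of the paired difference, if that is what was meant, and correct or explain the 27, since the stated inputs give 24.
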